## Methods/design

### Main objectives

The main objectives of this study are as follows:To assess the feasibility of a brief psychosocial intervention based on cognitive behavioral therapy (CBT) and early PC in advanced cancer patients, including patient acceptance and satisfaction.To assess the impact of the intervention on symptoms of depression at 90 days after randomization and to compare the differences between the intervention groups and the control group and between the intervention groups.

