### Data collection and randomization

The psychological intervention will be conducted by psychologists trained for the study. Data collection will be conducted by a team of research coordinators from the Center for Research Support at Barretos Cancer Hospital (BCH; Barretos, SP, Brazil).

A trained member of the Center for Research Support, not involved in data collection or statistical analysis, was assigned to handle the randomization process, using tables of random numbers. The study participants will be randomized (1:1:1) into arms A, B or C. Randomization will be based on blocks of six patients and will be stratified as follows: breast, gynecological, gastrointestinal, urological, head and neck, and thoracic. The study arms will be as follows:Arm A (experimental): psychosocial plus early PC, including five weekly psychosocial interventions based on CBT plus early PC (a first medical consult at the Palliative Care Service will be scheduled for 2 to 3 weeks from the study inclusion date and every 3 to 4 weeks thereafter).Arm B (experimental): early PC (a first medical consult at the Palliative Care Service will be scheduled for 2 to 3 weeks from the study inclusion date and every 3 to 4 weeks thereafter).Arm C (no intervention): standard oncologic care.

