### Primary outcome measures

The primary outcome measures are listed below:Descriptive results about the feasibility of the interventions (the average duration of each intervention session in minutes, the number of absences and the reasons for non-attendance in the intervention groups, the accrual rate, and the reasons for ineligibility).Changes in satisfaction with care from baseline according to the FAMCARE-Patient scale at days 45, 90, 120 and 180.Changes in depression symptoms from baseline according to the HADS-D and PHQ-9 at day 90.

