### Secondary outcome measures

The secondary outcome measures are listed below:Changes in depressive symptoms from baseline according to the HADS-D and PHQ-9 at days 45, 120 and 180.Changes in anxiety symptoms from baseline according to the HADS-A at days 45, 90, 120 and 180; the proportion of patients who believe that their cancer is curable as measured using an adapted instrument to evaluate patient awareness (all of the patients will have incurable advanced cancers; therefore, patients who claim that their disease is curable will be interpreted as not being adequately aware of their prognosis).Changes in cancer symptoms from baseline according to the ESAS-br at days 45, 90, 120 and 180; changes in QL from baseline according to the EORTC QLQ-C15-Pal at days 45, 90, 120 and 180.

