### Statistical analysis

The demographic and clinical pretreatment characteristics of the patients will be compared between the study arms (A *versus* B *versus* C) using the analysis of variance (ANOVA) test for independent measurements (for the continuous variables) and the chi-squared test (for the categorical variables). Data normality will be assessed using the Shapiro-Wilk test [26] and the data distribution patterns. Cohen’s *d* effect size will be calculated according to the mean difference between the two treatment evaluations divided by the pooled standard deviation of the sample. The analysis of repeated measurements will be performed for each type of outcome at 45, 90, 120 and 180 days after randomization, and these results will be compared to those at the beginning of the study. The effect size will be calculated between Arms A versus C, B versus C, A versus B, and also Arms A plus B versus C. The effect size between the groups will be considered small (0.20 to 0.49), moderate (0.5 to 0.79) or large (≥0.80) [27]. The scores for depression and anxiety symptoms and QL will be compared over time using a mixed model analysis of variance (ANOVA) for repeated measurements. The disease awareness scores and the rate of end-of-life invasive procedures will be compared using the chi-squared test (or Fisher’s exact test). A *P* value <0.05 will be considered statistically significant. The statistical software SPSS v.21 will be used for the statistical analyses.

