### Sample size calculation

For the a priori power analysis, GPower software v.3.0 (Heinrich-Heine-Universität, Düsseldorf, Germany) [28] was used to calculate the minimum sample size required for this study. Cohen’s effect size was randomly considered moderate to large (Cohen’s d = 0.65) according to decreased HADS-D and PHQ-9 scores when the experimental arms (A or B) were compared with the control group (Arm C). The estimated sample size would be 39 participants in each arm for a difference between independent means, α of 5% (two-tailed hypothesis) and a power of 80%. Each group shall have a total of 50 patients considering a monitoring loss rate of 25% to 30%. A study of this size will have 80% power to detect differences between Arms A plus B versus Arm C on the depression symptom scores associated with an effect size of 0.5 and alpha of 5%. This study is preliminary in nature, and a key objective of this study is to assess the feasibility and acceptability of a new clinical intervention. Furthermore, this study aims to assess the magnitude of the effect of adding a psychosocial intervention to early PC, which has not been determined according to the literature and would be useful in planning a future definitive phase III trial.

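### The primary depression outcome is the day-90 change, but the only between-arm test named is a repeated-measures ANOVA over time, with no day-90 contrast and with baseline as a comparison point, not a covariate

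*Protocol article*

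**What the plan says.** All references are to the Protocol article.

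- **Time point.** Main objectives includes "To assess the impact of the intervention on symptoms of depression at 90 days after randomization", with comparisons of each intervention group against control and of the two intervention groups with each other. Primary outcome measures lists "Changes in depression symptoms from baseline according to the HADS-D and PHQ-9 at day 90".
- **Other visits.** Secondary outcome measures lists "Changes in depressive symptoms from baseline according to the HADS-D and PHQ-9 at days 45, 120 and 180".
- **Sizing.** Sample size calculation gives 39 per arm "for a difference between independent means" at d = 0.65, two-sided 5% and 80% power. This is raised to 50 per arm for an expected loss of 25% to 30%.
- **Test.** Statistical analysis states that the depression, anxiety and quality-of-life scores "will be compared over time using a mixed model analysis of variance (ANOVA) for repeated measurements". On the repeated measurements at 45, 90, 120 and 180 days it adds that "these results will be compared to those at the beginning of the study".
- **Effect sizes.** The same section plans Cohen's d for A versus C, B versus C, A versus B and A plus B versus C, without singling out a primary visit.
- **Strata.** Under Data collection and randomization: "Randomization will be based on blocks of six patients and will be stratified as follows: breast, gynecological, gastrointestinal, urological, head and neck, and thoracic". Statistical analysis does not mention them.

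**The concern.** The outcome and the sample size both point to one comparison: arm means at day 90. The named test points elsewhere. A repeated-measures ANOVA reports by default a group effect averaged over visits and a group-by-time interaction. Neither is the day-90 difference. The first dilutes a day-90 effect with the other visits, and the second can be significant because of a difference at a secondary visit. The section sets P < 0.05 as its criterion, so an omnibus result could be taken for a result on the primary outcome.

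The second part is precision. The text describes follow-up scores as compared with those at the start, which is a change-score use of baseline. Using the baseline score as a covariate gives a smaller variance for the same patients. That matters in a trial whose Discussion names small sample size as the main limitation and which aims to estimate effect magnitude for a later phase III trial.

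**Working it through.** **1. The plan's own figure.** With d = 0.65, two-sided α = 0.05 and a two-sample t-test (noncentral t), power is 79.9% at 38 per arm and 80.9% at 39. The stated 39 reproduces, and it is the sample size for a single two-mean comparison.

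**2. Evaluable patients.** 50 × (1 − 0.30) = 35 and 50 × (1 − 0.25) = 37.5, so 35–37 per arm.

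**3. What the omnibus tests respond to.** Assumptions, none from the document: two arms of 39, five visits including baseline, compound symmetry with correlation ρ, effects in score SD units. The group main effect uses the mean effect over visits divided by √((1+4ρ)/5). The interaction F has noncentrality (n/2)·Σ(deviation from mean effect)²/(1−ρ), with 4 and 4(2n−2) degrees of freedom.

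| Effect at days 0, 45, 90, 120, 180 | Test | ρ = 0.3 | ρ = 0.5 | ρ = 0.7 |
|---|---|---|---|---|
| 0, 0.30, 0.65, 0.30, 0.30 | group | 53% | 42% | 34% |
| same | group-by-time | 46% | 61% | 85% |
| 0, 0.65, 0.65, 0.65, 0.65 | group | 93% | 83% | 74% |
| same | group-by-time | 68% | 84% | 98% |
| 0, 0.65, 0, 0, 0 | group-by-time | 68% | 84% | 98% |

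Example, second row at ρ = 0.5: mean effect 1.55/5 = 0.31, sum of squared deviations 0.212, noncentrality 19.5 × 0.212/0.5 = 8.27, power 61%. The last row has no day-90 effect at all, yet the interaction is usually significant. In the third and fourth rows the effect is constant after baseline, and the omnibus tests do not always lose power. The difficulty is that they answer a different question.

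**4. Baseline as a covariate against a change score.** With equal variance s² at both visits and correlation ρ between baseline and day 90:

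- Var(change) = 2(1−ρ)s²
- Var(baseline-adjusted) = (1−ρ²)s²
- Ratio = (1+ρ)/2 = 0.65, 0.75, 0.85 for ρ = 0.3, 0.5, 0.7

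The power gain depends on the SD to which d = 0.65 refers, so both readings are shown. In change-score SD units, adjustment turns d into 0.65·√(2/(1+ρ)). In score SD units, d becomes 0.65/√(2(1−ρ)) for the change score and 0.65/√(1−ρ²) with adjustment. Power at 35–37 per arm:

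| ρ | Change score, d in change SD | Adjusted | Change score, d in score SD | Adjusted |
|---|---|---|---|---|
| 0.3 | 76–79% | 91–93% | 62–64% | 80–82% |
| 0.5 | 76–79% | 87–89% | 76–79% | 87–89% |
| 0.7 | 76–79% | 83–85% | 93–95% | 96–97% |

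**5. Strata.** The document gives no between-site variance, so no figure can be put on adjusting for tumour site.

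**The case against.** The strongest reply is that this is a condensed journal article. It lists no model terms at all, and covariates and stratum terms are commonly left to a fuller protocol or analysis plan. That stands, and it limits the point. A reader might infer several stronger claims that the document does not support:

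- **That the analysis is unadjusted.** This would be read from silence. The text neither includes nor excludes covariates.
- **That baseline is not used.** It is: outcomes are changes from baseline, and follow-up is compared with the start. It is only not named as a covariate. A change-score analysis is valid in a randomised trial, so the issue is efficiency, not bias.
- **That day 90 cannot be tested.** Day 90 is among the analysed visits, a contrast can be drawn from the model, and effect sizes are planned for the relevant arm pairs. The contrast is unspecified, not precluded. Nor does the text say that inference will rest on the omnibus tests.
- **That patients missing any visit will be dropped.** This applies only if the classical SPSS repeated-measures procedure is used. The wording could equally mean the MIXED procedure, which keeps incomplete cases.
- **That leaving out the strata invalidates the inference.** Omitting them normally makes it conservative, and the gain from including them cannot be quantified.

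The Discussion also says that statistical significance matters less than the main objectives. That lowers the stakes for a P value. It does not remove the need for a defined day-90 estimate, because day-90 depression is itself a main objective and effect magnitude is a stated aim.

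**Conclusion.** The point holds in a limited form. What the document does state does not line up: a day-90 primary outcome, a sample size for one two-mean comparison, and a between-arm test over time with no day-90 contrast attached. Baseline adjustment beats the change score on either scaling of d. In power, the gain runs from about 2–3 percentage points (ρ = 0.7, score SD units) to about 18 (ρ = 0.3, score SD units). In change-score SD units it is about 6 to 15 points.

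These figures rest on an assumed ρ of 0.3 to 0.7, equal variances at baseline and day 90, and 35–37 evaluable per arm. The omnibus results also rest on assumed effect profiles and compound symmetry, and show only that those tests need not track day 90. This should be changed because it is cheap and sharpens a main objective; it does not show that the planned analysis is invalid.

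**What to change.** State the primary depression analysis, separately for HADS-D and PHQ-9, as a linear mixed model fitted by REML (SPSS MIXED) to all available post-baseline visits. Its terms are arm, visit, arm-by-visit, baseline score and tumour-site stratum, with the covariance structure named. Designate the day-90 contrasts A versus C, B versus C, A versus B and A plus B versus C, with 95% confidence intervals, as the primary results, and label the contrasts at days 45, 120 and 180 secondary. Naming the procedure also settles how patients with a missed visit are handled.

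The cost is a change of wording in the protocol or analysis plan, made before the data are analysed. Baseline scores and tumour site are already collected, the four arm comparisons are already listed, and the software is already named. No new data or patients are needed.

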**Methods/design:**

The primary objective is to evaluate the feasibility of psychosocial intervention and PC in patients with advanced cancer. The patients will be submitted to a series of brief psychosocial interventions that are based on cognitive behavioral therapy, and patient acceptance and satisfaction will be assessed. In addition, the impact of these interventions on depressive symptoms will be evaluated. A randomized, open-label, phase II trial with two intervention arms and a control group will be conducted. Patients who are started on palliative chemotherapy and who meet the inclusion criteria will be enrolled. The study participants will be recruited from the outpatient oncology clinics at Barretos Cancer Hospital and will be randomized into one of the following three treatment arms: Arm A, which will include five weekly psychosocial interventions based on CBT in combination with early PC; Arm B, which will include early PC only; and Arm C, which will include standard oncologic care. The Hospital Anxiety and Depression Scale (HADS), the Patient Health Questionnaire (PHQ-9), the Edmonton Symptom Assessment System (ESAS-br), the Family Satisfaction with End-of-Life Care (FAMCARE)-Patient scale, and the Disease Understanding Protocol will be used for data collection. The patients will answer these questionnaires at baseline and 45, 90, 120 and 180 days after randomization.

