### Secondary objectives

The secondary objectives of the study are as follows:To assess the impact of the interventions on symptoms of depression at 45, 120 and 180 days after randomization and to compare the differences between the intervention groups and the control group and between the intervention groups.To assess the impact of the interventions on anxiety symptoms at 45, 90, 120 and 180 days after randomization and to compare the differences between the intervention groups and the control group and between the intervention groups.To assess the impact of the interventions on the QL scores at 45, 90, 120 and 180 days after randomization and to compare the differences between the intervention groups and the control group and between the intervention groups;To assess the impact of the interventions on symptom scores (pain, fatigue, nausea, drowsiness, anorexia, dyspnea, and insomnia) at 45, 90, 120 and 180 days after randomization and to compare the differences between the intervention groups and the control group and between the intervention groups.To assess the differences in disease awareness at 45, 90, 120 and 180 days after randomization in the three arms of the trial.To assess the differences in the number of invasive procedures at the end of life, such as intensive care unit admissions and chemotherapy during the last 14 to 28 days of life, between the treatment arms.

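### Disease awareness is compared by a chi-squared test that leaves out the baseline answer; this is valid but gives up power if a patient's answers are at least moderately correlated over time

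*Protocol article*

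**What the plan says.** **Outcome.** Secondary outcome measures defines awareness as "the proportion of patients who believe that their cancer is curable as measured using an adapted instrument to evaluate patient awareness". It is a proportion and is not worded as a change from baseline, unlike the depression, anxiety, symptom and quality-of-life outcomes beside it.

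**Objective.** Secondary objectives: "To assess the differences in disease awareness at 45, 90, 120 and 180 days after randomization in the three arms of the trial".

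**Data.** The abstract says that "the Disease Understanding Protocol will be used for data collection" along with the other instruments, and then: "The patients will answer these questionnaires at baseline and 45, 90, 120 and 180 days after randomization". The Measures section calls what appears to be the same instrument the Disease Awareness Protocol. The baseline answer is therefore collected.

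**Analysis.** Statistical analysis: "The disease awareness scores and the rate of end-of-life invasive procedures will be compared using the chi-squared test" (or Fisher's exact test). Other patient-reported outcomes are treated differently: "The scores for depression and anxiety symptoms and QL will be compared over time using a mixed model analysis of variance". Awareness is not in that list. A general sentence in the same section reads "The analysis of repeated measurements will be performed for each type of outcome at 45, 90, 120 and 180 days after randomization", and adds that results will be set against those at the start of the study. It names no method for awareness.

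**The concern.** The method is fixed in the text, so this is not a detail left to an unseen analysis plan. The text names a two-way table test for an outcome measured in the same patients before and after randomization. A belief asked repeatedly of the same person will plausibly resemble its own earlier value. If it does, the baseline answer explains part of the variation in the follow-up answer, and a test that leaves it out is less precise than it could be.

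With under 40 evaluable patients per arm and a yes/no outcome, precision is scarce. If 60% believed in cure at baseline, the chance difference between two arms of 37 would have a standard deviation of √(2 × 0.6 × 0.4 / 37) = 0.114, about 11 percentage points. When answers are correlated, part of that imbalance passes into the unadjusted follow-up difference. The trial is meant to inform a later phase III design, so a sharper estimate has value even where significance matters less.

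**Working it through.** **1. The plan's own figure.** Sample size calculation takes d = 0.65 with "α of 5% (two-tailed hypothesis) and a power of 80"%, and reports 39 per arm for depression scores.
- Normal approximation: n = 2(1.960 + 0.842)² / 0.65² = 37.2, so 38.
- Noncentral t: power is 0.7985 at n = 38 and 0.809 at n = 39, so 39. The figure reproduces.

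No power is stated for awareness.

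**2. Evaluable patients.** 50 per arm less 25% to 30% leaves 37.5 to 35. I use 37 per arm.

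**3. Assumptions (none is in the documents).** Follow-up belief in cure is 60% v 35%. Baseline belief is 60%, or 85% as a sensitivity case. The baseline and follow-up answers are cut from a bivariate normal variable with latent correlation ρ from 0 to 0.8. With 60% at baseline, ρ of 0.6 to 0.8 corresponds to a correlation between the yes/no answers (phi) of about 0.41 to 0.59.

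**4. Plain chi-squared power by formula.** With mean proportion 0.475:

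z = [0.25√37 − 1.96√(2 × 0.475 × 0.525)] / √(0.6 × 0.4 + 0.35 × 0.65) = (1.521 − 1.384) / 0.684 = 0.20, giving power 0.58.

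**5. Stratified test.** With k indexing the two baseline answers, CMH = [Σ(aₖ − n₁ₖmₖ/nₖ)]² / Σ[n₁ₖn₀ₖmₖ(nₖ − mₖ) / (nₖ²(nₖ − 1))], compared with 3.84. Here aₖ counts believers in the experimental arm, mₖ counts all believers, and n₁ₖ and n₀ₖ are the arm sizes in stratum k.

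**6. Simulated power, 37 v 37 (40,000 trials per cell).**

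| ρ | 60% at baseline: chi-squared → CMH | gain (points) | 85% at baseline: chi-squared → CMH | gain (points) |
|---|---|---|---|---|
| 0 | 0.576 → 0.577 | 0 | 0.576 → 0.576 | 0 |
| 0.2 | 0.576 → 0.584 | 1 | 0.574 → 0.579 | 0.5 |
| 0.3 | 0.577 → 0.592 | 1.5 | 0.577 → 0.588 | 1 |
| 0.4 | 0.575 → 0.606 | 3 | 0.577 → 0.596 | 2 |
| 0.6 | 0.567 → 0.645 | 8 | 0.577 → 0.618 | 4 |
| 0.7 | 0.577 → 0.687 | 11 | 0.573 → 0.628 | 5.5 |
| 0.8 | 0.574 → 0.735 | 16 | 0.575 → 0.645 | 7 |

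Separate runs of 20,000 put the gain at ρ = 0.6 at about 7 points, so 7 to 8 is within simulation error.

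**7. Arms A plus B v C (74 v 37), 60% at baseline.** Power goes from 0.713 to 0.736 at ρ = 0.4, from 0.713 to 0.776 at 0.6, and from 0.712 to 0.855 at 0.8.

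**8. Type I error (37 v 37, 60% in both arms).** 0.046 to 0.048 for chi-squared and 0.048 to 0.051 for CMH.

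**9. Check under other rates (39 v 39, common odds ratio across baseline strata, phi specified directly).**
- 50% v 25%: 0.643 → 0.634 at phi 0, 0.638 → 0.664 at 0.3, 0.635 → 0.730 at 0.5.
- 40% v 20%: 0.499 → 0.481 at phi 0, 0.510 → 0.523 at 0.3, 0.504 → 0.581 at 0.5.

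The largest loss at 39 v 39 in these two settings is 1.8 points, at phi 0. The largest anywhere in this set was 2.5 points, at 78 v 39 with 70% v 45% and phi 0.

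**The case against.** **The test is not wrong.** A chi-squared or Fisher's test on a randomized proportion is standard and holds its size. A reader might infer that ignoring baseline biases the comparison. It does not: chance imbalance is already allowed for in the 5% error rate. This objection stands and limits the point to efficiency.

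**The gain rests on assumptions.** A reader might infer that a substantial loss of power is certain. The documents give neither rates nor a correlation, and at low correlation nothing material is lost. Arm A's sessions also explain the diagnosis and current health status, which could weaken the link between baseline and later answers in that arm. This stands too, and is why the full range is shown.

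**The general sentence may cover it.** The section announces an analysis of repeated measurements for every type of outcome, with reference to the start of the study. A reader might infer from the chi-squared sentence that the plan runs four separate visit tests with no overall comparison. The text does not say so: the chi-squared sentence names no visits, and the general sentence points the other way. However, the general sentence does not bring the baseline answer into the between-arm awareness test, so the two need reconciling.

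**The stakes are low.** Awareness is secondary, no power is claimed for it, and the Discussion ranks statistical significance below the main objectives. That sets the priority. It does not argue against a change that needs no new data.

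**The simulated contrasts have two groups.** The objective concerns three arms. The direction should carry over, but the figures apply to pairwise and pooled contrasts only.

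**Conclusion.** The point holds as an optional improvement. The named test for disease awareness discards a baseline answer that the trial collects. It remains valid, so the cost is precision only.

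Under the assumed 60% v 35% with 37 per arm, stratifying by the baseline answer gains about 0 to 3 points of power at latent correlation up to 0.4. At 0.6 to 0.8 it gains about 7 to 16 points with 60% believing in cure at baseline, or about 4 to 7 points with 85%. The downside is about 2 points if the answers are uncorrelated. Every one of these sizes depends on rates and correlations that the documents do not give. The point does not extend to end-of-life invasive procedures, which have no baseline value.

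**What to change.** For disease awareness only, replace the chi-squared test with one of these:
- a Cochran-Mantel-Haenszel test stratified by the baseline answer; or
- a logistic model fitted by GEE over the visits, with arm, visit, arm-by-visit and baseline answer.

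Apply it to the arm contrasts already planned (A v C, B v C, A v B, and A plus B v C) and report odds ratios or risk differences with 95% confidence intervals. Keep Fisher's exact test for very sparse tables, and leave the end-of-life procedures comparison as it is.

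State in the same paragraph how the general repeated-measurements sentence applies to awareness. If a main visit is wanted for this outcome it has to be named, because the Main objectives tie day 90 to depression only.

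The cost is a change of wording, best made before awareness is compared by arm. No extra patients, visits or data are needed.
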